### Randomisation, stratification and blinding

Randomisation to the intervention group receiving the MIS or the control group takes place on the level of departments to avoid contamination between health care workers receiving the MIS or not. Prestratification was performed based on two criteria, creating four groups: workers have contact with patient (material) versus workers have no contact with patient (material); and high vs. low risk for developing hand eczema, assessed by the occupational physician. Based on the sequence of inclusion, randomisation was performed in strata of two by an independent researcher. For practical reasons the randomization will be performed before baseline measurements. Workers are not informed about the outcome of the randomisation and the design of the study i.e. the existence of the two groups (control and intervention). The department managers are explicitly requested not to inform their workers about this. It is impossible to blind researchers, occupational nurses and department managers for the intervention.

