#### Step 3 Collecting solutions

After the three most important problems are chosen, the working group brainstorms about solutions to overcome these problems using again the nominal group technique. The solutions gathered are prioritized according to criteria of existence, feasibility, complexity and the solving capability of the solution. The manager judges whether the costs of the solutions are feasible; the person from the infection prevention department decides whether the solutions are in line with the hand hygiene procedures. The solutions are prioritized using the same method as in step 2, resulting in a top three of solutions.

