#### Step 5 Implementation of the solutions

The members of the working group implement the solutions, supported by the trained nurse. This implementation phase takes place between meeting two and three. To improve the effectiveness of the implementation process, role models are introduced named Dermacoaches. Dermacoaches are workers from the working group who followed a special training about (the prevention of) hand eczema and are trained on how to promote and enhance the implementation of the solutions and adherence to the guidelines. The Dermacoaches stimulate and motivate their colleagues to be aware of their risk behaviour during work and try to decrease the problems with adherence to the recommendations at the department. They also receive a Dermacoach toolkit which contains posters. These posters are used as reminders to the recommendations for their colleagues at the department and are placed at sinks or other relevant places [26]. Other contents of the toolkit are posters and e-mails with the top-3 problems and solutions prioritized by the working group; and presentations on hand eczema, which they can use during work meetings. Further, the role model assists the trained occupational nurse with the education to the other workers at the department. This is described under the heading *'the education program'*.

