#### Secondary outcome measures

The three questions from NOSQ-2002 only measure the presence or absence of hand eczema, without taking into account the symptoms related to it [33,34]. Therefore, a symptom-based questionnaire is added to measure the symptoms of hand eczema every three months [19].

The impact of hand eczema on the worker's disease-specific quality of life is measured using the DLQI [35]: a 10-item scale which measures the impact of skin diseases on several physical, psychological and social aspects of daily life. For this study we use the Dutch version of the DLQI adapted by Evers et al. [36]. It will be measured at baseline, after 6 and 12 months.

Workers' global assessment of the health of their hands and patients' global assessment of eczema will be assessed at baseline and after 6 and 12 months, using a 11-point Likert scale based on the NOSQ-2002 (question D12) [33].

Skin exposure during work time is measured using an adopted version of the NOSQ-2002 [33,34]. It will be measured at baseline and after 6 and 12 months.

The actual use of preventive measures is measured with a modified version of the NOSQ-2002. The modifications are necessary, because questions have to be in accordance with the specific work environment of the workers. Further, the researchers monitor whether the preventive measures are used or not. In addition to self reported use, information is collected at the department level about the actual use of protective measures like gloves, use of disinfectants and use of barrier creams. This information is gathered by the purchasing department and the pharmacy of the participating hospitals. Both the questions from the NOSQ-2002 and purchase data will be collected every 3 months.

Sick leave is measured by using the PRODISQ [37]: one general question on sick leave and three questions about sick leave due to hand eczema. Work productivity is measured using a single item question from the WHO Health Productivity Questionnaire [38,39] and three single item questions from PRODISQ [37]. All but one question on work productivity are measured on a 11-point Likert scale. Health care costs related to hand eczema are collected with respect to the economic evaluation. All these questions will be assessed every 3 months.

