### Statistical analyses

All analyses are performed according to the intention to treat principle. Most analyses are performed at worker level. Two analyses are performed: 1) a crude analysis with the outcome variable measured at follow-up as the dependent variable adjusted for the outcome, measured at baseline, and 2) an analysis as above but adjusted for potential covariates (e.g. gender, age, type of work, history of hand eczema, and skin exposure). Effects of the intervention will be checked for effect modification (gender, type of exposure, number of preventive skin measures implemented). Generalised estimation equations (GEE) are used to analyse long-term results (i.e. 12 months after baseline). Furthermore, analyses at department level are performed by the use of multilevel analysis.

For all analyses a two-tailed significance level of < 0.05 is considered statistically significant. The multilevel statistical analyses are performed with MlwiN 2.0; linear and logistic regression analyses are performed with SPSS 15.0 (SPSS Inc. Chicago, Illinois, USA), and GEE analyses is performed with STATA version 7.0 (College Station, TX).

Considering the episodic nature of hand eczema, the use of transition models is necessary. In these models, the presence of hand eczema in the past three months is incorporated. The probability of getting hand eczema in workers with no hand eczema and the probability of getting no hand eczema in workers with hand eczema are modelled simultaneously by means of a logistic mixed model as is done in a study with a comparative design on low back and neck pain [32]. Transitions models will be conducted using the gllamm procedure in Stata version 10.0.

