### Methodological considerations

A weakness of this is study is the risk for underreporting. Hand eczema is not a disorder that is considered to be a problem by health care workers, because many consider their hand eczema as a part of their job and are therefore not alarmed by it [23]. The workers who do recognize the problem of their hand eczema may, as a result, not report their eczema. It could therefore be difficult to measure a change in hand eczema in general and between the intervention and control group. Considering the large number of participants in this study, and the high work load of participants, we chose to optimise feasibility by measuring hand eczema by self report rather than an examination of the hands by a physician. A second weakness may be the forming of the working group. Ideally, the workers participating in the working group are role models at the department and are an example to their colleagues. However, we can only partly control the selection of workers and even then the right workers can refuse, leaving the department with a suboptimal composition of the working group. Third, randomisation was performed at department level to avoid contamination, but it is not possible to rule out contamination completely since intervention and control departments will be located in the same hospital. However, participants are not informed about the design of the study i.e. they do not know of the existence of a control and intervention group. In that way the contamination is minimized. That this study focuses not only on primary, but also on secondary prevention, can be considered as a fourth weakness. Workers with symptoms are probably more likely to comply with the recommendations, than workers with no symptoms at all. As a result, the effect of the intervention can be different for the two types of workers.

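### The effect-modification list includes the number of measures implemented, which the intervention itself produces, and leaves out hand eczema at baseline

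*Protocol article*

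**What the plan says.** The Statistical analyses section names three modifiers: "Effects of the intervention will be checked for effect modification (gender, type of exposure, number of preventive skin measures implemented". The same section opens with "All analyses are performed according to the intention to treat principle".

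Other sections fix when and how measures come to be implemented:

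- Randomisation, stratification and blinding: "For practical reasons the randomization will be performed before baseline measurements".
- Step 3: "The solutions are prioritized using the same method as in step 2, resulting in a top three of solutions".
- Step 5: "The members of the working group implement the solutions, supported by the trained nurse", and "This implementation phase takes place between meeting two and three".
- Secondary outcome measures: "The actual use of preventive measures is measured with a modified version of the NOSQ-2002". These data are collected every 3 months.

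On workers with and without symptoms, Methodological considerations says: "As a result, the effect of the intervention can be different for the two types of workers". In the Statistical analyses section, baseline outcome and history of hand eczema appear as adjustment terms and not as modifiers. That section also plans transition models in which onset among workers without eczema and recovery among workers with eczema are fitted together.

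**The concern.** Effect modification by a characteristic fixed before allocation compares randomised arms within each level of that characteristic. A count that the intervention changes does not allow this. Workers or departments at a given count in one arm are not the counterparts of those at the same count in the other. The result would be a dose-response statement that readers could take for a subgroup finding protected by randomisation.

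Meanwhile the contrast for which the authors themselves give a reason, primary versus secondary prevention, has no arm-by-baseline-status test. The three named modifiers would be checked, and the one argued for in the Discussion would not.

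**Working it through.** The plan states no figure on this point, so the check sets the passages side by side and then illustrates the mechanism.

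**1. Timing.** Randomisation precedes baseline. Meeting one is about 1 month after baseline and meeting two 1 month later, so at about month 2. Meeting three follows 4 to 6 weeks after that. Implementation between meetings two and three therefore starts about 2 months after baseline, and Step 4 allows solutions that take more than 3 months. The count is post-randomisation and may still be changing at the 3-month questionnaire.

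**2. Reading (a): the count is of working-group measures.** Write A for arm (1 = intervention) and M for the count:

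logit P(eczema) = b0 + b1·A + b2·M + b3·A·M.

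Control departments have no working group, so M is undefined there, or 0 by convention. With M = 0 whenever A = 0, A·M equals M for every worker. Only b2 + b3 can be estimated, which is the slope of eczema on M within the intervention arm. There is no arm interaction to test. With a top three of solutions and about 30 expected working groups, the slope would rest on roughly 30 non-randomised units with M mostly between 0 and 3.

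**3. Reading (b): the count is of workers' own uptake.** M now exists in both arms, but the intervention changes it. I simulated 1,000 trials of 1,200 workers (600 per arm) for each row below, with every parameter assumed:

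- an unmeasured trait U (standard normal), such as motivation;
- M Poisson with log mean 0.3 + 0.5·A + 0.15·U + 0.35·A·U;
- logit P(eczema) = logit(0.24) + β·U, with no effect of A or M.

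The A×M term was tested by logistic regression at two-sided 0.05.

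| β (log odds per SD of U) | Rejections of a true null interaction | Mean interaction coefficient per measure |
|---|---|---|
| 0 | 5.0% | -0.006 |
| -0.3 | 7.6% | -0.047 |
| -0.5 | 12.1% | -0.074 |
| -0.8 | 30.1% | -0.133 |
| +0.5 | 10.4% | +0.067 |

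The Monte Carlo standard error near 5% is √(0.05 × 0.95 / 1000) = 0.7 percentage points. The model has no clustering and no adjustment for baseline eczema. It shows the direction of the fault and not its size in this trial.

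**4. What the transition models cover.** Follow-up at 3, 6, 9 and 12 months gives four transitions. The first conditions on the baseline state. The other three condition on the state at 3, 6 and 9 months, which the intervention may already have altered. The text states neither an arm effect for each transition nor an arm-by-baseline-status test.

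**5. Precision of a baseline-eczema interaction.** Let f be the share of workers with eczema at baseline. With equal arms and, as a simplification, equal outcome variance in both groups, Var(interaction) / Var(overall effect) = 1 / [f(1 − f)]. The only prevalence given is 24% over one year, so I take that as the upper end for a 3-month share and half of it as a lower value.

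- f = 0.24: 1200 × 0.24 = 288 workers; 1 / (0.24 × 0.76) = 5.48; the standard error is √5.48 = 2.34 times that of the overall effect.
- f = 0.12: 1200 × 0.12 = 144 workers; 1 / (0.12 × 0.88) = 9.47; the standard error is 3.08 times as large.

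The interaction can be estimated, but its power is limited.

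**The case against.** The strongest reply is that this is one item in a parenthesis of effects to be checked, in what is partly an implementation study. The process evaluation already asks whether prioritised measures were implemented. The wording may also refer to workers' own use of skin protection, which is recorded in both arms, so the claim that controls have no value would not hold. The ambiguity is real, and the point does not depend on resolving it: under either reading the count follows randomisation, and both readings fail, for different reasons.

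Four stronger inferences are tempting, and the documents do not support them.

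- **That eczema status is ignored.** It is absent from the modifier list but not from the plan. The transition models separate onset from recovery, and their first interval conditions on baseline state.
- **That the authors predict a different effect.** They say only that the effect can differ. What they call probable is a difference in compliance.
- **That the skin-exposure covariate has the same fault.** It is measured at baseline as well as later, and nothing indicates that follow-up values would be used for adjustment.
- **That the intention-to-treat statement is breached or the main result biased.** The primary comparison still follows allocation. The fault is confined to this one interaction.

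It is also fair to say that an article may leave further interactions to an analysis plan. That would excuse a missing list. It does not excuse a list that names an unsuitable variable. Finally, baseline eczema is itself recorded after allocation, in departments whose managers know their arm. It is therefore a better modifier than the count, but not a flawless one.

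**Conclusion.** The point holds in a limited form. The plan names as an effect modifier a variable that arises after randomisation and that the intervention is meant to change. An arm interaction on it is either not estimable (working-group measures) or open to spurious findings (workers' uptake). The false-rejection rates of 7.6% to 30.1% rest on assumed confounding, independent workers and no baseline adjustment. The planned adjustment for baseline outcome would remove whatever part of the confounding that outcome captures. No figure for this trial can be derived from the documents.

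The omission of baseline eczema is a lesser, linked point: an internal mismatch between the modifier list and the Discussion, partly met by the transition models. The primary analysis stands. The change is worth making because a misleading dose-response claim could otherwise be read as a trial subgroup result.

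**What to change.** In the Statistical analyses section:

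1. Remove the implemented-measures count from the effect-modification list. Define it (working-group measures or workers' own uptake) and report it in the process evaluation as an exploratory, non-randomised analysis.
2. Put in its place an interaction of arm with hand eczema in the past 3 months at baseline (yes/no). Label it exploratory because its power is limited and because baseline is recorded after allocation.
3. Add a sentence on how the transition models estimate the arm effect on onset and on recovery, noting that the conditioning state is post-randomisation after the first interval.

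The cost is wording only. Baseline eczema is already collected, and the process evaluation and the 3-monthly questionnaires already record implementation and use.

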### Economic evaluation

Cost-effectiveness of the multifaceted implementation strategy will be evaluated from both the societal perspective and the employers' perspective. Both direct and indirect costs will be measured and valued. Indirect costs are not related to health care, but are costs in paid and unpaid labour as a consequence of sickness, sick leave, disability and/or death of a productive person. The indirect costs for production losses due to sick leave are calculated by using the Human Capital and Friction costs method [43]. For the latter method, the Dutch guidelines for economic evaluation is used [44]. The direct health care costs are calculated by using tariffs for the costs of health care professionals and market prices for the value of medication. Costs for the education, role model training and working groups are calculated by using the hourly wages. The direct non-health care costs, are calculated by using the information obtained from the cost questionnaires and shadow prices.

Bootstrapping [45] is used for comparison of mean direct, indirect and total costs between the two groups. Confidence intervals are obtained by bias corrected and accelerated bootstrapping. Cost-effectiveness ratios are calculated by dividing the difference between the mean costs of the interventions by the difference between the mean effects of the interventions. The bootstrapped costs effects pairs are graphically presented on a cost-effectiveness plane. Acceptability curves are calculated in order to show that the probability of the intervention is cost-effective at a specific ceiling ratio. Furthermore, sensitivity analyses are performed.

### Process evaluation

The process of the MIS is evaluated in five ways.

First, the working group is asked for their opinions on 1) the content and process of the working group meeting as a whole, 2) the specialised occupational nurse's competence, 3) their expectations towards the implementation and the effectiveness of the prioritised measures on the adherence to the recommendations.

Second, Dermacoaches are asked for their opinions about 1) the Dermacoach training as a whole, 2) the added value of the training as a role model to improve the implementation process and to improve the actual use of preventive measures, 3) their experiences/perceived effectiveness of being a role model.

Third, all workers of the intervention departments are asked about satisfaction, barriers and facilitators regarding the educational program and if they are aware of prioritised organisational measures and whether these measures are implemented at the department. Further they are asked whether they received the leaflet containing the recommendations for the prevention of hand eczema and their opinion on this leaflet.

Fourth, all members of the working group receive a questionnaire with the following questions: 1) whether the prioritised organisational measure(s) are implemented, 2) to identify and describe possible barriers and facilitators during the implementation of the measure(s). One worker of the working group is invited for a semi-structured interview in which the implementation process is discussed. The content and structure of the interview is based on the answers given in the questionnaires of all working group members.

Fifth, the department manager is also sent a questionnaire and is also invited for a semi-structured interview. The department manager is asked: 1) whether the prioritised organisational measure(s) are implemented, 2) to identify and describe possible barriers or facilitators during the implementation of the measure(s).

## Discussion

Hand eczema is a problem in the health care setting, because of the high prevalence among the workers in this occupational setting [5]. The problems are related to the burden for the individual worker, the employer and the society [8,10-14]. In this study, the effectiveness of a combination of several strategies for the prevention of hand eczema among health care workers will be investigated.

### Theoretical framework

Fleuren et al [46] developed a framework for innovation processes. According to this framework implementation can be affected by four constructs: characteristics of the socio-political context, the organization, the adopting person, and the innovation. In total, 50 determinants are identified to fit in one of these constructs. Depending on the nature of the determinant, the influence can be facilitating or impeding. The innovation strategy, which in this study is the MIS, can influence these determinants. Each aspect of the MIS targets one or more of the determinants indentified by Fleuren et al [46].

First, the socio-political context is taken into account by using the working groups. The working group forms solutions to overcome problems related to the implementation of the recommendations. The socio-political context can be a barrier for implementing the solutions. The working groups takes the socio-political context into account and adapts the solutions to this context. In that way implementation can be enhanced, making sure the socio-political context is not a barrier for implementation.

The working group also plays a part in influencing the characteristics of the organization. A participatory approach in decision making is a facilitating factor for implementation [46]. This participatory working group is formed out of members of the organization, e.g. the department of a hospital. They make sure that the solutions for the barriers to implementation do not conflict with the culture of the organization. Further, the education sessions will heighten the available expertise in relation to the innovation. Another determinant of the organization our intervention could have an influence on is on the presence of an opinion leader. This person influences opinions of others in the organization. The Dermacoaches will influence their colleagues to change their opinion towards the recommendations in a positive way.

The characteristics of the user are influenced by almost all parts of the MIS. The role models give support to their colleagues to use the recommendations and they perform the desired behaviour. In a study on hand hygiene compliance, the latter have shown to be important for enhancing adherence [14]. The education provides the workers with knowledge and skills needed to use the recommendations. The perceived ownership on the implementation of the recommendations is heightened by the working group. Further, the attitude of the workers is influenced by the education sessions.

Finally, the working group is important when considering the characteristics of the innovation. It is important that users, in this case the health care workers, are involved in the development of the innovation. Further, the working group makes sure that the solutions are compatible with the existing work procedures. Education to the workers can enhance the clarity of the recommendations, otherwise the lack of knowledge can form a barrier to the use of the recommendations.

